### 5.2 Study visits

Study encounters will take place over a 12-month period and do not incur any additional visits beyond standard of care active surveillance (Fig 3).

**Fig 3 pone.0295994.g003:**
[figure not shown]
Schedule of RECONCILE study visits.

*Visit 1 (baseline)*

The baseline visit consists of two encounters: a standard of care MRI prostate and a subsequent tissue donation visit at the time of standard of care NHS prostate biopsy. At the biopsy encounter, research blood, urine and prostate tissue will be collected.

Research data including baseline medical history and patient reported outcome (PRO) questionnaires will be collected on or before the standard of care biopsy visit. Baseline medical history review may take place over the telephone.

Participants enrolling to RECONCILE following participation in the ReIMAGINE Risk or PLiS studies will not be required to donate research blood, urine or prostate tissue at baseline. Instead they will consent to data and sample sharing from ReIMAGINE Risk or PLiS to RECONCILE.

*Follow-up PSA visits (3, 6 and 9 months)*

Following the baseline visit, clinical results will be provided in a standard of care NHS prostate cancer clinic. If active surveillance remains a suitable management option, the participant will proceed to interval 3 monthly PSA testing and clinic review as per national guidance. PSA kinetic data will be collected prospectively for research and entered into the study database.

*Interval (exit) visit (12 months)*

Interval (exit) investigations will take place 12 months after baseline tissue collection and consists of two standard of care encounters: an MRI prostate visit and subsequent targeted transperineal prostate biopsy. Again, research blood, urine and prostate tissue will be collected during the standard of care biopsy visit. PRO questionnaires will be posted to participants ahead of the biopsy visit and can be returned to study staff either by post or in person. Participants enrolled in the PLiS study will be invited to donate a semen sample at the time of study completion. This will be collected at home and returned to the study laboratory by post.

*Suspected progression*

Interval investigations, and exit from the study, may occur prior to the 12-month mark if there is suspicion of progression during PSA follow up. As is usual practice, standard of care mpMRI will be expedited and exit research samples collected (PROs, blood, urine, prostate tissue +/- semen) should the patient proceed to standard of care prostate biopsy.

*Non-visit*

Access to standard of care diagnostic biopsy tissue will be sought once the NHS centre has completed all necessary diagnostic evaluation. Formalin-fixed paraffin-embedded (FFPE) tissue blocks and haematoxylin and eosin (H&E) stained slides will be requested by RECONCILE study staff and anonymised H&E slides will be scanned using high resolution scanners and uploaded to the RECONCILE digital pathology database. Slices from standard of care FFPE tissue blocks will be collected in line with study standard of care operating procedures before returning all slides and blocks to the relevant NHS pathology department.

*Analyses*

Blood components (white blood cells, plasma, serum), urine, tissue and semen will undergo molecular analysis including genomic, mRNA expression and protein studies. These will include, but are not limited to, next-generation sequencing, whole-genome micro-array expression profiling, immunohistochemistry and immunofluorescence and ELISA tests.

*Long-term healthcare data linkage*

Consent will be sought to obtain long-term patient outcomes from national health records such as the Office for National Statistics, NHS Digital, Public health England and other applicable NHS information systems or national databases.

### 5.3 Definition of end of study

Following the collection of research samples (PROs, semen for PLiS participants, blood, urine and prostate tissue) at the exit visit men will revert to standard of care NHS follow up. No further study visits are required. This visit completes the end of the first phase of the RECONCILE study. Men will undergo study follow up for 4 to 8 weeks after the biopsy for pathology results to be collected.

Participants then transition to longitudinal follow-up via healthcare data linkage. This represents the second phase of the study for which no face-to-face visits are required. For the second phase of the study, the end of the study is defined as database lock.

## 6. Study interventions

RECONCILE will deeply phenotype MRI lesions of interest at baseline and one year. This will be achieved using additional targeted sampling (using visual-estimation) of the MR-visible lesion harbouring Gleason 3 + 4 cancer. Clinical (PRO and PMH), radiomic and fluidic biomarker (blood, urine, semen) data and samples will also be collected at baseline and exit.

### 6.1 Patient reported outcome questionnaires

Participants will be asked to complete three prostate cancer specific health-related quality of life and symptom severity questionnaires at the time of baseline and exit visits, these include the:

Expanded Prostate Cancer Index Composite-26 (EPIC-26)European Organisation for Research and Treatment of Cancer Quality of Life Questionnaire-C30 (EORTC QLQ-C30)Memorial Anxiety Scale for Prostate Cancer (MAX-PC)

Participants’ height, weight, ethnicity, medical history and family history of prostate cancer will be recorded at the time of enrolment.

### 6.2 MRI databank

Multiparametric MRI will be performed as standard of care [4]. Reporting will be according to study SOPs and include Likert and PI-RADS scales documented within a structured electronic case report form (eCRF). Lesions, and the prostate itself, will be contoured and segmented prior to upload to the study image repository, hosted by UCL.

### 6.3 Blood sample collection

Between 50 and 100ml of blood will be collected from each consenting study participant by a trained phlebotomist or RECONCILE Clinical Trial Practitioner during the baseline and exit visits. Venepuncture and sample collection will be performed in accordance with the RECONCILE Blood Sampling SOP. The required samples are outlined in Table 2. Whole blood samples will be processed by a trial Laboratory Technician or Clinical Trial Practitioner at the study affiliated UCL laboratory. Details of sample processing are outlined in Appendix I.

**Table 2 pone.0295994.t002:** Blood samples to be collected during the RECONCILE study baseline and exit visits.

Order of draw (by collection tube)	Number of tubes to be collected	Volume per tube (ml)
EDTA	1	10
SST	1	8.5
Streck^TM^	1	10
EDTA	1	10
PAXgene® Blood RNA	1	2.5
EDTA	1	10
Extra EDTA (optional)	0–6	10

Between 50 and 100 ml of blood will be collected from each consenting study participant by a trained phlebotomist or RECONCILE Clinical Trial Practitioner during visit 1 and once again at exit from the study. Venepuncture and sample collection will be performed in accordance with the RECONCILE Blood Sampling SOP. The required samples (to be collected both at baseline and once again at exit) and order of draw is outlined in Table 2.

### 6.4 Urine sample collection

An early morning urine sample will be collected in line with the study SOP by study practitioners during the baseline and exit visit. Urine collection will always take place prior to prostate biopsy. The pseudonymised samples will be transferred to a study affiliated UCL laboratory and logged within the study FreezerPro database. Both unspun and centrifuged urine will be stored within the study biobank. Spun samples will be centrifuged using a one-step process (3300g for 20 mins, with a break, at room temperature). Both centrifuged and unspun urine will be stored at -80C as will the residual cell pellet.

### 6.5 Prostate tissue collection

Consenting patients will donate three additional cores of prostate tissue at the time of their baseline standard of care prostate biopsy. At exit, participants will donate a further 3 biopsy tissue cores, or five additional cores if there is a new lesion on mpMRI. Cores 4 and 5 will be collected from the highest scoring, greatest volume new lesion.

We do not anticipate that collection of additional tissue cores for research will increase the likelihood of side effects or adverse events relative to standard of care biopsy alone. The risks and adverse outcomes of prostate biopsy quoted within the RECONCILE patient information sheet are outlined in Table 3. Research cores will be targeted using visual-estimation to areas of interest identified on pre-biopsy mpMRI. Research cores will only be attempted after all required standard of care diagnostic biopsies have been collected.

**Table 3 pone.0295994.t003:** Side effect profile of a targeted transperineal prostate biopsy as stated in the RECONCILE study patient information sheet.

Side effect	Proportion of men	Duration
Pain/discomfort in back passage	Almost all	Temporary for 1–2 days
Burning when passing urine	Almost all men	Self-resolving, 1–3 days
Bloody Urine	Almost all	Self-resolving, 1–7 days
Bloody Sperm	Almost all	Lasting up to 3 months
Poor erections	1–2 in 100	Temporary for 1–6 weeks
Infection of skin/urine	1–2 in 100	7 days with treatment with antibiotics
Infection of skin/urine needing admission and intravenous antibiotics	Less than 1 in 500	7–14 days with treatment with antibiotics. Rarely up to 28 days of antibiotics after leaving hospital.
Difficulty passing urine requiring catheter placement for up to a week. A catheter is a soft plastic tube placed into the bladder to drain urine.	1 in 100	3–7 days
Bruising of skin	Almost all	Self-resolving, 7–14 days
Bruising spread to scrotum	1 in 100	Self-resolving, 7–28 days

All cores will be collected in line with the study Tissue Collection SOP. The first and second research cores will be collected from the centre of the lesion with the highest Likert / PIRADS score and greatest volume (lesion 1). Lesion volume will be determined by MRI reporting.

The third research core will be collected from an area of non-suspicious (Likert / PIRADS score 1 or 2) tissue. Should new MRI lesions be visible at the time of exit from the study (minimum Likert / PIRADS score 4), two additional tissue cores (Cores 4 and 5) may be collected from the centre of the new highest scoring, greatest volume lesion. Table 4 summarises the location from which to collect each prostate biopsy core.

**Table 4 pone.0295994.t004:** Prostate tissue sampling locations for the RECONCILE study.

Research Core	Lesion to target	Area within lesion to target	Casette colour
Core 1	Lesion with highest PIRADS / Likert score and greatest volume (lesion 1)	Centre of the lesion	Pink
Core 2	Same lesion as above (lesion 1)	Centre of lesion 1	Green
Core 3	Contralateral nonsuspicious area	Any non-suspicious radiological area, either contralateral lobe or TZ if bilateral lesions or diffuse changes in bilateral lobes	Yellow
Core 4 (optional)	New radiological lesion with the highest PIRADS/LIKERT score at interval assessment (lesion 2)	Centre of lesion 2	Any colour, labelled as Core 4
Core 5 (optional)	New radiological lesion with the highest PIRADS/LIKERT score at interval assessment (lesion 2)	Centre of lesion 2	Any colour, labelled as Core 5

The location of each prostate core will be recorded within a study CRF (Fig 4) and each core placed within a colour coded pathology cassette before being placed within PAXgene® tissue fixative. Samples will be fixed in PAXgene® Tissue Fix reagent for at least 2–24 hours. Cores are then treated with PAXgene® Tissue Stabalizer concentrate and ethanol for at least 2 hours. All pseudonymised samples will be logged to the FreezerPro database and stored at -80°C following stabiliser treatment. All biological samples are processed and stored in line with the RECONCILE Laboratory Manual.

**Fig 4 pone.0295994.g004:**
[figure not shown]
RECONCILE study Tissue Collection Form (eCRF).

### 6.6 Semen sample collection

PLiS participants will be invited to donate a semen sample at the time of their exit visit. The sample will be collected at home (ahead of prostate biopsy) and returned to the study affiliated laboratory by post or courier. Their baseline comparator sample will be shared from the PLiS study which collects pre-biopsy semen samples in prostate biopsy-naive men.

### 6.7 Formalin-Fixed Paraffin Embedded (FFPE) tissue blocks and haematoxylin and eosin (H&E) slide collection

In addition to the prostate tissue cores collected for research, standard of care diagnostic pathology FFPE tissue blocks and H&E slides will be requested from the participating centre once all diagnostic evaluation is complete. Pseudonymised H&E slides will be scanned using the Hamamatsu Nanozoomer S360 high-throughput digital slide scanner at a resolution of 0.23 μm/pixel. Digitalised, pseudonymised slides will be stored within a dedicated RECONCILE database held securely on UCL servers.

Digitalisation will facilitate computer-based assessment of morphological features. RECONCILE tissue technicians will also collect tissue slices from standard of care FFPE tissue blocks to provide additional tissue for analysis. All FFPE tissue blocks and H&E slides will be returned to the relevant NHS pathology department. All processes will be conducted in accordance with study SOPs.

### 6.8 Standard of care PSA levels

Participants will undergo standard of care monitoring with three-monthly PSA blood testing at the recruiting NHS site. Each standard of care PSA value reported during active participation in the study will be entered into the study database.

## 7. Outcomes

### 7.1 Primary outcome

The primary outcome of the RECONCILE study is the proportion of concordant pairs of molecular and radiological progressors at exit from active follow up (usually at 12 months).

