### 3.1 Primary objective

The primary objective is to estimate the association of molecular changes with radiological progression events of small, localised Gleason 3 + 4 tumours visible on mpMRI.

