### 8. Statistical analysis

The primary statistical analysis will be to estimate the association of match‐paired binary responses (molecular and radiological progressors) since the results of the two tests are not independent. For McNemar’s test of paired proportions using the Miettinen normal approximation with a two‐sided significance level of 0.05, a sample size of 60 achieves a power of at least 0.8 when the discordant proportions are 0.05 (5%) and 0.25 (25%) of the total number. The ratio of progressors will inform the precision of the IC for the molecular analysis. Study results will be shared in peer reviewed journal articles.

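### The primary outcome is a raw proportion of concordant pairs, which does not by itself measure the association that the primary objective and analysis set out to estimate

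*Protocol article*

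**What the plan says.** Section 3.1 of the protocol article states: "The primary objective is to estimate the association of molecular changes with radiological progression events". Section 1.2 gives the same aim, the abstract describes the study as powered for an association, and section 8 says that the primary analysis estimates the association of the two paired binary results.

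Section 7.1 defines the primary outcome differently, as "the proportion of concordant pairs of molecular and radiological progressors at exit from active follow up".

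Section 8 names one test, "McNemar’s test of paired proportions using the Miettinen normal approximation". It claims power of at least 0.8 with 60 men at a two-sided 0.05 level "when the discordant proportions are 0.05 (5%) and 0.25 (25%) of the total number". These two discordant proportions are the only planning figures for the table.

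Section 4.3 commits to a contingency table of radiological progression (R+/R-) by molecular change (M+/M-) to examine how the two relate. The article gives no expected rate of R+ or M+.

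**The concern.** The objective and the outcome are different quantities. A proportion of agreeing pairs depends on how common each kind of progression is as well as on whether the two are related. When few men progress, most pairs agree because neither classification is positive, and concordance can be high with no relation at all. When progression is common on both measures, the same concordance can reflect a strong relation.

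At stake is the headline result. A trial that follows section 7.1 to the letter reports a percentage from which a reader cannot tell whether molecular change and radiological progression are associated.

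The wording also leaves open which pairs count. It can mean pairs in which the two classifications agree (M+R+ or M-R-), or only pairs in which both progress (M+R+).

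**Working it through.** **Inputs.** From section 8: n = 60, two-sided alpha 0.05, discordant proportions 0.25 and 0.05. The article does not say which discordant cell is which. I take M+R- = 0.25 and M-R+ = 0.05; swapping them exchanges the margins and leaves concordance, odds ratio and kappa unchanged. The M+R+ proportion, called a, is not stated and is varied as an assumption.

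**The plan's own figure.** With total discordance 0.25 + 0.05 = 0.30 and difference 0.25 - 0.05 = 0.20, the Miettinen second-order approximation gives

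power = Phi[(-1.96 × 0.30 + 0.20 × √(60 × 0.30)) / √(0.30² - 0.20² × (3 + 0.30)/4)] = Phi(0.2605/0.2387) = 0.862.

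The claim of at least 0.8 holds under the method named and is not in dispute.

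**Concordance under the both-agree reading.** Concordance = 1 - 0.05 - 0.25 = 0.70, whatever the split of the 0.70 between M+R+ (a) and M-R- (0.70 - a).

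**Association for a given a.**
- Margins: M+ = a + 0.25 and R+ = a + 0.05.
- Odds ratio = a(0.70 - a)/(0.25 × 0.05) = a(0.70 - a)/0.0125.
- Chance-expected concordance pe = (M+)(R+) + (1 - M+)(1 - R+).
- Kappa = (0.70 - pe)/(1 - pe).

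Independence requires a(0.70 - a) = 0.0125, so a = 0.0183 or 0.6817.

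| a | R+ | M+ | Concordance | Chance-expected | Odds ratio | Kappa |
|---|---|---|---|---|---|---|
| 0.0183 | 6.8% | 26.8% | 70% | 70.0% | 1.0 | 0.00 |
| 0.05 | 10% | 30% | 70% | 66.0% | 2.6 | 0.12 |
| 0.10 | 15% | 35% | 70% | 60.5% | 4.8 | 0.24 |
| 0.20 | 25% | 45% | 70% | 52.5% | 8.0 | 0.37 |
| 0.35 | 40% | 60% | 70% | 48.0% | 9.8 | 0.42 |
| 0.6817 | 73.2% | 93.2% | 70% | 70.0% | 1.0 | 0.00 |

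The odds ratio peaks at 9.8 (a = 0.35) and falls to 0 at a = 0. As counts of 60 in the order M+R+, M+R-, M-R+, M-R-, the first row is about 1, 15, 3, 41 and the fourth is 12, 15, 3, 30.

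**McNemar's test.** It uses only the discordant counts, 15 against 3: z = (15 - 3)/√18 = 2.83, exact p = 0.0075. The result is the same in every row, because the test compares the two progression rates. It therefore does not supply the missing information on association.

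**Concordance with both margins fixed.** Concordance = 1 - R+ - M+ + 2a, which rises with a. At R+ = 25% and M+ = 45% it is 0.30 + 2a: 52.5% under independence (a = 0.25 × 0.45 = 0.1125), 70% at odds ratio 8 (a = 0.20), and 80% when every R+ man is also M+ (a = 0.25).

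**The both-progress reading.** The outcome is then a itself and the 70% does not arise. The table shows odds ratio 1 at a = 1.8% and again at a = 68.2%. Likewise, a share of 20% goes with odds ratio 8 at margins of 25% and 45%, but with odds ratio 1 if M+ is 45% and R+ is 0.20/0.45 = 44.4%. This share also needs the margins.

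**The case against.** Several objections are fair.

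First, 5% and 25% are a scenario for the power statement and not a forecast, so nothing says the trial will observe 70%. This stands; the scenario serves here only to show that one concordance value is compatible with very different associations.

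Second, a reader might infer that concordance is 70% whether or not the two are related, as a general property. The documents do not support that. It needs the discordant cells held fixed and the margins left free, and exact independence needs one of two particular pairs of margins. In the other rows shown, 70% exceeds chance. What remains is that concordance alone does not tell the reader which row applies.

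Third, a reader might infer that the trial cannot answer its primary question. That goes too far. Section 4.3 plans the full two-by-two table, from which margins, odds ratio, kappa and chance-expected concordance all follow, and section 8 says association will be estimated.

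Fourth, one might set the interval for a 70% concordance, ± 1.96 × √(0.7 × 0.3/60) = ± 11.6 points, against the chance level and call any overlap chance agreement. That is not a test of association, because the chance level is estimated from the same men. At R+ 15% the interval of about 58% to 82% includes the chance value of 60.5%, yet the odds ratio is 4.8, with chi-square p = 0.031 and Fisher p = 0.054.

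Fifth, the choice of agreement statistics is commonly left to an analysis plan. True, but the point does not rest on an omission: the article states both an objective and an outcome, and they are different quantities.

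**Conclusion.** The point holds as a mismatch between the stated primary outcome and the stated primary objective. Under the both-agree reading and the plan's own discordance figures, concordance is 70% at odds ratio 1 (R+ 6.8%, M+ 26.8%) and at odds ratio 8 (R+ 25%, M+ 45%), with kappa 0 and 0.37. The margins are illustrative assumptions, since the article states none. Under the both-progress reading the 70% does not apply, but the conclusion is the same.

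The defect is that the outcome in section 7.1 is uninterpretable alone. It is not that the data will be unable to address the objective, and it is not an error in the stated power. The change should be made before analysis, because it concerns the headline result and costs little.

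**What to change.** Reword section 7.1 so that the primary outcome is the association between molecular change and radiological progression at exit, taken from the section 4.3 contingency table and expressed as an odds ratio with an exact 95% confidence interval. State which pairs count as concordant. Report raw concordance only as a supporting figure, beside its chance-expected value from the observed margins or with kappa.

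The cost is a rewording of section 7.1 and the matching change to the published outcome definition. The table already planned supplies every cell, so no further data or participants are needed. The power figure in section 8 describes a comparison of the two progression rates and should not be carried over as power for the odds ratio.

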### 7.2 Secondary outcomes

Secondary objectives span imaging, pathology, molecular and clinical features and include:

*Imaging*

Time to radiological progression on standard of care MRI scan (i.e. evidence of MRI change either at planned standard of care MRI scan at one year from baseline, or on an expedited standard of care prior to thisQuantitative and qualitative assessment of MRI lesion(s) imaging characteristicsQuantitative imaging features (MRI and derivative) of the MRI lesion(s), a radiological progression ring (region of interest of the periphery within the MRI lesion at follow up which did not harbour abnormal signal at baseline), if present, and the rest of the prostate at different time pointsQualitative imaging features (MRI and derivative) of MRI lesion(s), a radiological progression ring (if present) and the rest of the prostate at different time pointsQuantitative imaging characteristics of MRI lesion(s), a radiological progression ring (if present) and the rest of the prostate at different time points and stratification according to radiological progression vs non progression

*Histology*

Qualitative and quantitative histologic composition of cancer lesions and their surrounding tissueHistological heterogeneity of cancer, both qualitatively and quantitatively

*Molecular analysis*

The molecular index (as defined in section 4.4.1 of this protocol) of the cancer lesion in question, as well as the surrounding peritumoral and normal tissueQualitative and quantitative analysis of urinary and seminal biomarkersQualitative and quantitative analysis of inflammatory infiltrate in the cancer lesion, peritumoral and normal tissueAnalysis of blood-based biomarkers related to immune surveillance and inflammatory cytokinesQualitative and quantitative analysis of immune related pathways

*Clinical data*

Proportion of patients who transition to active treatment, stratified according to the timing and nature of treatmentProportion of patients eligible for each treatment option at baseline and follow-upRate of metastasis at specified time points during follow upConcordance rate between histological and radiological progressionConcordance of PRECISE score reporting among study radiologistsPatient reported outcomes at different time points using prostate cancer-specific health-related quality of life and symptom severity scores using the Expanded Prostate Cancer Index Composite-26 (EPIC-26), the European Organization for Research and Treatment of Cancer-Quality of Life Questionnaire-C30 (EORTC QLQ-C30) and the Memorial Anxiety Scale for Prostate Cancer (MAX-PC)

